#### Aim 2: Intervention effect on TB and HIV clinical outcomes

Composite TB treatment outcomes will be summarized as rates within each intervention arm. Adjusted differences in composite TB outcome rates between intervention arms will be estimated using multivariable Poisson regression models with random effects for study site and counsellor. All-cause mortality over the 12-month follow-up period will be assessed using time-to-event methods. The cumulative mortality function will be estimated using the Kaplan–Meier product-limit estimator, stratified by intervention arm and accounting for clustering by study site and counsellor. Adjusted differences in mortality risk between intervention arms will be estimated using multivariable Cox proportional hazards regression models incorporating random effects for study site and counsellor. Similar survival analysis methods will be applied to evaluate time to sputum-culture conversion among participants with microbiologically confirmed TB.

Differences in HIV-related outcomes, including viral suppression and antiretroviral therapy adherence, will be evaluated using adjusted multivariable logistic regression models, with appropriate specification of random effects and covariates.

Although the study is not explicitly powered to detect differences within individual disease subgroups, all analyses will be conducted stratified by disease cohort, including TB-only, HIV-only, and TB–HIV co-infected participants. This stratified analytic approach will allow for an assessment of the consistency of the BI intervention’s effectiveness across clinically relevant populations. Findings from these subgroup-specific analyses will be interpreted cautiously and considered exploratory in nature. The results are expected to inform hypotheses regarding differential effects and to identify potential gaps requiring targeted investigation in future, adequately powered studies.

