#### Outcomes

Primary outcome (Specific Aim 1): Our primary outcome is alcohol use at six months as measured by the alcohol biomarker Phosphatidyl Ethanol (PEth).(42) PEth will be collected using dried blood spots. In the initial proposal, the primary outcome measure was based on alcohol self-report, using the Time Line Follow Back (TLFB) interview.(43, 44) At the HATHI DSMB meeting on May 30, 2024, the DSMB recommended changing to PEth due to observed under-reporting of alcohol use on the TLFB by participants compared to PEth.

Secondary alcohol outcomes: We will examine the following secondary outcomes of PEth at Month 6and 12:
PEth as a binary variable at different thresholds of alcohol use: PEth ≥ 20; ≥50; ≥ 200Total drinking days in the last 30 days measured using TLFB (count)AUDIT score (Cut off: ≥8 for men, ≥ 6 for women), and continuousComposite TLFB and PEth: Total drinking days using TLFB and PEth ≥ 20; ≥50; ≥ 200Composite AUDIT score and PEth: AUDIT ≥ 8 / ≥ 6 men/women & PEth ≥ 20; ≥50; ≥ 200

Other secondary clinical outcomes (Specific Aim 2) are described in Tables 2 and 3 and defined further in Appendix 1.

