
Secondary alcohol-related outcomes include self-reported alcohol consumption assessed using the 30-day TLFB interview. The number of drinking days over the prior 30 days will be analysed as a count outcome, conceptualized as arising from a binomial distribution, Binomial (30, *p*), where *p* represents the proportion of days on which alcohol consumption occurred. The independent effect of the intervention on the proportion of drinking days will be evaluated using adjusted random effects generalized linear models with a logit link function, incorporating random effects for study site and counsellor to account for within group correlation. Differences between intervention arms in the number of self-reported heavy drinking days over the prior 30 days, as measured by the TLFB, will be assessed using multivariable generalized linear random-effects logistic regression models, incorporating random effects for study site and counsellor to account for within group correlation. Intervention effects on other secondary alcohol-related outcomes derived from PEth and AUDIT measures will similarly be evaluated using multivariable random-effects logistic regression models, as appropriate for the outcome distribution. All adverse events (AEs), including serious adverse events (SAEs), and deaths will be monitored and recorded in accordance with the study protocol and established study procedures. AEs and SAEs will be summarized descriptively by study arm using counts and proportions. For comparative analyses between intervention arms, outcomes with binary response distributions will be analysed using multivariable logistic regression models, while count-based AE outcomes will be analysed using multivariable Poisson regression models (or alternative count models if indicated), with appropriate adjustment for clustering and covariates.

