**Tuberculosis**			
TB treatment failure, default or mortality (composite)			X
TB treatment failure: smear or culture positive at 5 months		X	X
TB treatment default: interruption of TB treatment for ≥ 2 consecutive months		X	X
All-cause mortality			X
TB treatment adherence		X	
Retention in TB care		X	

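### The TB composite reads as a yes/no outcome but is assigned a random-effects Poisson model with no person-time offset or robust variance; fitted with the usual errors, it tends to be conservative

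*Protocol article*

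**What the plan says.** The Aim 2 part of the Statistical method section says: "Composite TB treatment outcomes will be summarized as rates within each intervention arm". Arms are then compared by "multivariable Poisson regression models with random effects for study site and counsellor". It mentions no exposure time, offset, dispersion correction or variance estimator.

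Table 2, in its tuberculosis block, lists "TB treatment failure, default or mortality (composite") with a single mark at 12 months. Two of the components are defined there: "TB treatment failure: smear or culture positive at 5 months" and "TB treatment default: interruption of TB treatment for ≥ 2 consecutive months". The third is death from any cause. The Outcomes section says that the Aim 2 outcomes are "defined further in Appendix 1", which is not at hand.

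Other binary outcomes are handled differently. For adverse events, the Aim 1 section says that "outcomes with binary response distributions will be analysed using multivariable logistic regression models" and keeps Poisson models for counts. In the Aim 2 section, viral suppression and ART adherence "will be evaluated using adjusted multivariable logistic regression models".

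**The concern.** As Table 2 describes it, each participant with TB either has or does not have the composite by 12 months. A Poisson likelihood sets the variance equal to the mean, p, whereas a yes/no outcome has variance p(1−p). Random effects for site and counsellor can add variance but cannot take this excess away. With likelihood-based errors, the interval for the arm effect is then wider than the data warrant and the test rejects too rarely.

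The article gives no reason for leaving its own practice of logistic models for binary outcomes. At stake is the precision of a named clinical hypothesis. No power is stated for it, and the number of participants with TB has become smaller than first planned, because an HIV-only group was added within the same 450 (Protocol amendments).

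**Working it through.** **Inputs.** The article gives no event risk, sample size or power for the TB composite, so there is no stated figure to reproduce. Assumed: composite risk 10–40%, two-sided test at 5%. Allocation is 1:1 (Trial Design). The ICC of 0.04 comes from the Sample size section, where it applies to PEth.

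**Variance of the log risk ratio, n per arm.**
- Poisson, likelihood-based: 1/(n·p0) + 1/(n·p1)
- Binomial: (1−p0)/(n·p0) + (1−p1)/(n·p1)

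**Equal risks in both arms.** The ratio of standard errors is 1/√(1−p), and the actual type I error is 2·[1 − Φ(1.96/√(1−p))].

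| Assumed p | SE ratio | Actual type I error |
|---|---|---|
| 10% | 1.054 | 3.9% |
| 20% | 1.118 | 2.8% |
| 30% | 1.195 | 1.9% |
| 40% | 1.291 | 1.1% |

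**Power with an assumed risk ratio of 0.6.** Let r be the SE ratio. A test with 80% power under the binomial variance has Φ(2.8015 − 1.96·r) under the Poisson errors (2.8015 = 1.960 + 0.8416).

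| Control vs intervention | n × variance, Poisson | n × variance, binomial | r | Power |
|---|---|---|---|---|
| 10% vs 6% | 26.67 | 24.67 | 1.040 | 77.7% |
| 20% vs 12% | 13.33 | 11.33 | 1.085 | 75.0% |
| 30% vs 18% | 8.89 | 6.89 | 1.136 | 71.7% |
| 40% vs 24% | 6.67 | 4.67 | 1.195 | 67.7% |

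For 30% vs 18%: 2.8015 − 1.96 × 1.136 = 0.575, and Φ(0.575) = 71.7%. At a fixed, assumed size of 150 per arm with 20% vs 12%, power is 46.0% with the binomial variance and 39.5% with the Poisson errors.

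**Do the random effects remove the excess?** A random-intercept Poisson likelihood was fitted to simulated binary data: 304 participants and 8 counsellors (both assumed), ICC 0 or 0.04, 1000 runs per setting. The ratio below is mean SE over the empirical SD of the estimate.
- Counsellors seeing both arms, no true effect: 1.01–1.08 at 10% risk, 1.11–1.15 at 20%, 1.22–1.25 at 30%. Rejection was 1.5–3.4% instead of 5%.
- Counsellors seeing both arms, risk ratio 0.6, ICC 0.04: 0.97, 1.12 and 1.09 at control risks of 10%, 20% and 30%. At 10% no inflation is visible.
- Counsellors nested in arm, ICC 0, risk 20% or 30%: 1.16–1.20, again too wide.
- Counsellors nested in arm, ICC 0.04, risk 20% or 30%: 0.85–0.86, with rejection about 11%. Here the errors are too small.

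**The case against.** Four objections carry weight.

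- **The variance estimator is not stated.** A reader might infer that the plan has chosen likelihood-based errors and that its intervals are therefore wrong. The article does not say so. Those errors are the usual default for a random-effects Poisson fit, but an analysis plan may specify a robust variance, and a suitable one removes the problem. The point is conditional on this.
- **Rates could mean events per person-time.** Rates with a Poisson model are a standard person-time analysis. The single 12-month mark in Table 2 does not exclude it, since all-cause mortality carries the same mark and is analysed by time-to-event methods. With an offset for time to first event, the fault disappears. Against this reading, no offset is mentioned, failure is a status at a fixed month, and the same section names survival methods for mortality and sputum conversion but not for the composite. The reading is less likely but remains open.
- **The direction can reverse.** Only the intervention arm receives counselling sessions, so some nesting of counsellors in arm is plausible. The simulation shows that nesting with few clusters can make the errors too small. The article gives neither the number of counsellors nor whether they see both arms.
- **The size is easily overstated.** All risks are assumed, and near 10% the effect is small. For 30% vs 18%, a reader might equate the excess variance with discarding 22% of participants (1 − 6.89/8.89). That matches interval width only, since the estimate itself loses no precision. By power the equivalent is about 18%: 1 − ((1.96 + 0.575)/2.8015)² = 0.18. Nor does the article make this its main comparison: PEth is primary, and the composite is secondary.

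What remains is a positive choice of model that fits poorly with the outcome as tabulated and with the article's own practice.

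**Conclusion.** The concern holds in conditional form. The article assigns a count model to what reads as a binary composite and names nothing that would correct its variance. Fitted as written with the usual errors, and with counsellors seeing both arms, the standard error is overstated by roughly 5–20% at assumed risks of 10–30%. Power then falls from 80% to about 78–72% for a risk ratio of 0.6. The consequence is a conservative comparison on a secondary outcome; the PEth primary analysis is untouched.

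The documents do not support the stronger statement that the reported intervals will be too wide. That would need a binary outcome, no offset, likelihood-based errors and no dominant clustering by arm, and the article does not settle all four. If counsellors are nested in arm and few, clustering may be the larger problem and act in the opposite direction.

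**What to change.** State that the composite is analysed with the random-effects logistic model used for the other binary outcomes, keeping the site and counsellor effects. Report standardised risks by arm with a risk ratio or risk difference, and call the summary a proportion.

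An acceptable alternative is modified Poisson with a robust variance that also respects counsellor clustering. A sandwich at participant level alone would correct the binary variance but ignore the counsellor correlation that the plan sets out to model.

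If person-time rates are intended, keep Poisson, and state the offset and the date on which each component (failure, default, death) counts as an event.

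The cost is one or two sentences and slight extra analysis work for the standardisation. Changing to a logistic model does not by itself cure the problem of few counsellors nested in arm.

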## Background and Rationale

India has the highest incidence of TB in the world, accounting for 26% of all new cases globally, with 48,000 among People With HIV (PWH).(1, 2)  India also ranks third globally in absolute HIV burden, with 2.6 million PWH and 64,000 new HIV infections in 2024.(3) PWH are 14–18 times more likely to develop TB, and TB is the leading cause of death among PWH.(4) Unhealthy alcohol use encompassing heavy use, heavy episodic (binge) drinking, and alcohol use disorders (AUD),(5) triples the risk of TB in the general population, increasing susceptibility to primary infection and reactivation, and also leads to poor outcomes including decreased treatment adherence, treatment default, treatment failure, relapse, and death.(6–10)

In India, alcohol use is on the rise.(11, 12) Our prior work in India has demonstrated 1) a high prevalence of unhealthy alcohol use among patients with TB, and 2) that unhealthy alcohol use is one of the major reasons for treatment default, failure, and mortality.(9, 10, 13, 14) Among PWH, unhealthy alcohol use is associated with HIV transmission, decreased use of and adherence to ART, lower viral suppression, decreased engagement and retention in care, more rapid HIV disease progression, and mortality.(15–21)

Individual-level behavioral alcohol interventions have been associated with significantly decreased HIV viral loads and increased medication adherence among PWH.(22) Such interventions among persons with TB show promise among people with TB but data are limited.(14, 23, 24) Further, despite the high burden of unhealthy alcohol use, behavioral interventions are not commonly available in TB and HIV care settings.

Brief, two to four session alcohol interventions, consisting of Cognitive Behavioral Therapy (CBT) and Motivational Enhancement Therapy (MET) are the most widely used and empirically supported behavioral interventions to reduce unhealthy alcohol use and alcohol-related harms and most frequently culturally adapted for low and middle income county (LMIC) use.(25–30) We have developed and tested culturally relevant brief counseling interventions for unhealthy alcohol use among PWH in Vietnam,(31) and for primary care settings in India.(32, 33) Maintaining the core components of these brief alcohol interventions, we have adapted them for use in HIV and TB clinical settings in India and now seek to test its effectiveness.

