#### Aim 4:

To measure incremental costs from health system and societal perspectives of integrated BI in TB and HIV settings.

We hypothesize that compared to usual care, BI will result in 1) lower alcohol use at six months (primary outcome), 2) decreased TB treatment default, failure or death, 3) increased TB medication adherence, 4) increased retention in TB care; and among PWH, 5) increased HIV-RNA suppression, 6) increased ART adherence, and 7) increased retention in HIV care.

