###### TB Measures:

TB outcomes of medication and appointment adherence will be measured using self-report, biomarkers and clinic records. We use the AIDS Clinical Trial Group (ACTG) adherence questionnaire to measure adherence. In addition, urine and blood samples will be collected to measure urine Isoniazid metabolites and TB drug levels respectively. Retention in care will be measured through clinic registration records and through study records. Sputum will be obtained to determine time to sputum conversion. TB treatment outcomes of cure, treatment failure, and recurrence will be abstracted from the TB treatment card.

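### Time to sputum-culture conversion takes over the mortality methods with no provision for death before conversion, a competing event; if such deaths are censored, the Kaplan-Meier proportion converted is somewhat too high

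*Protocol article*

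**What the plan says.** The statistical section for Aim 2 deals first with mortality: "All-cause mortality over the 12-month follow-up period will be assessed using time-to-event methods". The curve is specified as follows: "The cumulative mortality function will be estimated using the Kaplan–Meier product-limit estimator", by arm. The comparison is a Cox model with random effects for site and counsellor: "Adjusted differences in mortality risk between intervention arms will be estimated using multivariable Cox proportional hazards regression models". The section then turns to conversion: "Similar survival analysis methods will be applied to evaluate time to sputum-culture conversion among participants with microbiologically confirmed TB".

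Conversion is a planned outcome. The abstract lists it among the clinical outcomes, and the TB Measures section says "Sputum will be obtained to determine time to sputum conversion". Table 3 schedules cultures at baseline, weeks 2, 4 and 8, and month 6. Table 2, which lists outcomes and time points, has no row for it.

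Deaths are anticipated. The Background says that "unhealthy alcohol use is one of the major reasons for treatment default, failure, and mortality", and the hypotheses at the end of the Objectives include "decreased TB treatment default, failure or death". The article does not mention competing risks or cumulative incidence, and it gives no rule for a participant who dies unconverted. Its missing-data methods and censoring weights concern PEth and intervention dose.

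**The concern.** An estimator that is right for one outcome is carried over to another where its meaning changes. With all-cause mortality nothing competes with the event, so 1 minus Kaplan-Meier is the cumulative probability of death. With culture conversion, a participant who dies unconverted can never convert. Treated as censored, that participant is represented from then on by those still alive and unconverted, and is in effect credited with their later conversions. The curve then describes a hypothetical setting without deaths, and its height exceeds the proportion who actually convert.

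What is at stake is the absolute proportion converted in each arm and the visual gap between the curves. If one arm has more deaths before conversion, its curve is raised more, and the plotted difference departs from the difference in actual conversion. The Cox comparison does not share this fault: with deaths censored it estimates the cause-specific hazard ratio, a legitimate quantity provided it is labelled as such.

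**Working it through.** The protocol gives no conversion rate, death rate, event count or power for this outcome, so it has no figure to reproduce. All rates below are assumptions.

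**Inputs**
- Culture visits after baseline: weeks 2, 4, 8 and 26 (Table 3; month 6 taken as week 26).
- Assumed cumulative conversion in the absence of death: 30/50/75/95% (pattern A) or 20/40/70/90% (pattern B).
- Assumed weekly death hazard *h* while unconverted: 0.001 to 0.006.
- Assumed 100-150 participants with confirmed TB per arm, used only for standard errors.

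**Model.** Let *a* be the fraction alive and unconverted. In an interval of length Δ weeks, a(1 − exp(−hΔ)) die. At the visit, a fraction *p* of those remaining convert, where *p* is the conditional conversion probability. Then 1 − KM = 1 − Π(1 − p), and the cumulative incidence is the sum of the fractions converting.

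**Worked case: pattern A, h = 0.004.** The conditional probabilities are 0.30, 0.20/0.70 = 0.286, 0.25/0.50 = 0.50 and 0.20/0.25 = 0.80.

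| Visit | Die in interval | Convert at visit | Left unconverted |
|---|---|---|---|
| Week 2 | 0.80% | 29.76% | 69.44% |
| Week 4 | 0.55% | 19.68% | 49.21% |
| Week 8 | 0.78% | 24.21% | 24.21% |
| Week 26 | 1.68% | 18.03% | 4.51% |

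By month 6, 3.8% have died unconverted and 91.7% have converted. 1 − KM shows 95.0%, so the excess is 3.3 points. At week 8 the figures are 73.7% and 75.0%, an excess of 1.3 points.

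**Range**

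| Pattern | h | Died unconverted by month 6 | Excess at week 8 | Excess at month 6 |
|---|---|---|---|---|
| A | 0.001 | 1.0% | 0.3 | 0.9 |
| A | 0.002 | 1.9% | 0.7 | 1.7 |
| A | 0.004 | 3.8% | 1.3 | 3.3 |
| A | 0.006 | 5.6% | 2.0 | 4.9 |
| B | 0.001 | 1.1% | 0.4 | 0.9 |
| B | 0.002 | 2.2% | 0.7 | 1.7 |
| B | 0.004 | 4.4% | 1.4 | 3.4 |
| B | 0.006 | 6.5% | 2.1 | 5.0 |

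For scale, the SE of the month 6 proportion, √[CIF(1 − CIF)/n], is between 1.9 points (pattern A, lowest hazard, n = 150) and 3.6 points (pattern B, highest hazard, n = 100).

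**Check with constant hazards.** Here 1 − KM = 1 − exp(−λc·T), and the cumulative incidence is λc/(λc + λd)·[1 − exp(−(λc + λd)T)]. Assume 70% conversion by week 8 and 10% dead from any cause by week 26. Then λc = −ln(0.3)/8 = 0.1505 and λd = −ln(0.9)/26 = 0.0041. 1 − KM against cumulative incidence is 70.0% against 69.1% at week 8, and 98.0% against 95.6% at week 26. In this case 2.6% die before conversion. The direction is the same, and the excess again follows deaths before conversion, not deaths overall.

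**Arm contrast.** Take pattern A in both arms with h = 0.006 against 0.003 and equal conversion hazards. Deaths before conversion are 5.6% and 2.9%. 1 − KM shows 95.0% in both arms, while cumulative incidence is 90.1% and 92.5%, a difference of 2.4 points. The SE of that difference is 4.0 points at n = 100 per arm and 3.3 at n = 150, so the shift is 0.6-0.7 SE. If the same hazards applied to everyone, 1 − exp(−26h) gives six-month mortality of 14.4% against 7.5%.

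**The case against.** The strongest objection is that the article does not say deaths are censored. A reader might infer from the back-reference to Kaplan-Meier that they will be, but that is only the default. The word similar leaves room for another rule, such as keeping those who die in the risk set as non-converters to the end of the window, which would remove the problem. The analysis plan, not shown, may settle it. This stands, and it is why the point is conditional. It does not remove the point, because the article names an estimator by back-reference and does not adapt it to an outcome that death precludes.

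Second, the arm comparison rests on Cox, which remains valid as cause-specific. This stands; what is affected is the curve and the absolute proportions.

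Third, a reader might infer that usual care must be inflated more under the trial's own hypothesis, so that a benefit is hidden. The documents do not support that. The hypothesis concerns a composite that includes death, with no separate hypothesis on death, so which arm would be affected more is not known.

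Fourth, the larger figures need high mortality. The 5.6% against 2.9% contrast implies roughly 14% against 7.5% six-month mortality and a halved death hazard, neither of which the documents support. The eligibility criteria exclude people too ill to attend sessions and, in the TB cohort, reported drug-resistant TB, which points to lower mortality. This stands, and the contrast should be read only as an illustration.

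Finally, the outcome ranks low, and mortality and the TB composite are analysed separately, so deaths would not go unreported. This also stands.

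**Conclusion.** The point holds as a minor one. The plan extends mortality methods to culture conversion without providing for death as a competing event. If deaths before conversion are censored, 1 minus Kaplan-Meier overstates the proportion converted, by more in whichever arm has more of these deaths.

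The size cannot be determined from the documents. With assumed conversion of 90-95% by month 6, it is about 1 point if 1% die unconverted and about 3 points if 4% do. It is smaller at week 8, and negligible if early deaths are rare. Only deaths before conversion and up to the month 6 culture matter; the remaining deaths over 12 months do not. The distortion of the arm difference stays below one SE even in the high-mortality illustration.

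The Cox hazard ratio, the mortality analysis, the primary PEth analysis and the sample size of 450 are not called into question.

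**What to change.** State how deaths before conversion are handled. Report culture conversion by arm as Aalen-Johansen cumulative incidence with death before conversion as a competing event, for example at week 8 and month 6. Keep the Cox model for the arm comparison and label its hazard ratio cause-specific. Keep Kaplan-Meier for all-cause mortality.

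The cost is about one sentence of analysis wording and a standard software option. Deaths are already recorded, so no new data are needed. The trial is described as ongoing, so the sentence can be added before analysis. If the analysis plan already says this, it is enough to align the article's wording with it.

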### Eligibility Criteria

Inclusion Criteria:
Unhealthy alcohol use defined as Alcohol Use Disorders Identification Test (AUDIT) Score ≥ 8 in men / ≥ 6 in women;Age ≥ 18 years of age;Active TB (with or without HIV) defined as either:
a) Microbiologically confirmed TB (sputum AFB smear positive by microscopy or +GeneXpert at entry) orb) Clinical TB that is subsequently confirmed by Acid-Fast Bacilli (AFB) culture;Initiating TB therapy within 30 days of enrollment.

OR
Unhealthy alcohol use defined as AUDIT Score ≥ 8 in men / ≥ 6 in women;Age ≥ 18 years of age;HIV infection.

Exclusion Criteria:
In current treatment for unhealthy alcohol use;Unable to participate in intervention sessions either due to severity of medical illness, cognitive dysfunction or active psychosis;Pregnant (will refer directly to alcohol treatment);Household member of current study participant;TB Cohort only: Patients reported to have drug-resistant TB, multidrug-resistant TB (MDR-TB), or extrapulmonary TB (EPTB). (Note: People with HIV and EPTB are not excluded)

Eligible participants with 1) severe alcohol use disorder, determined by the Mini International Neuropsychiatric Interview (MINI) MINI DSM-V,(38) 2) a history of alcohol withdrawal, or 3) a Clinical Institute Withdrawal Assessment (CIWA)(39) score of 12 or greater, will first be evaluated by psychiatry faculty at study sites, BJGMC or DYPMC for medical clearance prior to enrollment due to risk of alcohol withdrawal.

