### Interventions:

#### Usual Care (UC):

Individuals randomized to the UC arm will receive provider advice to reduce or abstain from alcohol use and referral to alcohol treatment services at the provider’s discretion. In addition to usual care, at all visits, participants will also receive vital signs as part of the study to monitor blood pressure and pulse, and the CIWA will be performed to screen for alcohol withdrawal.

All participants, irrespective of assigned study condition, will receive standard of care for TB and HIV treatment, including 4-drug TB therapy and for PWH, ART. Individuals with TB randomized to UC arm will return for their routine TB treatment visits at weeks 4 and 8 where sputum will be collected per standard of care. They will have an additional study visit at week 2, where sputum will be obtained. PWH will receive standard of care delivered by the HIV clinic which includes monthly monitoring of ART side effects, clinical assessment, TB and other opportunistic infection evaluations, counseling for psychosocial and adherence support, CD4 count every 6 months, and viral load testing every 12 months.

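### Time to culture conversion is observed only in four visit intervals and its risk set does not require a positive baseline culture; a Cox model with usual tie handling would understate the hazard ratio

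*Protocol article*

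**What the plan says.** In the protocol article's section on Aim 2 (intervention effect on TB and HIV clinical outcomes), the mortality analysis comes first: "The cumulative mortality function will be estimated using the Kaplan–Meier product-limit estimator, stratified by intervention arm", followed by "multivariable Cox proportional hazards regression models incorporating random effects for study site and counsellor". Culture conversion then gets one sentence: "Similar survival analysis methods will be applied to evaluate time to sputum-culture conversion among participants with microbiologically confirmed TB". Tie handling and interval censoring are not mentioned.

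The TB block of Table 3 schedules pulmonary culture at baseline, weeks 2, 4 and 8, and month 6. The month 3, 4 and 12 cells are empty. The Usual Care section agrees with the early part of this schedule. It describes "routine TB treatment visits at weeks 4 and 8 where sputum will be collected per standard of care" and adds, for week 2, "They will have an additional study visit at week 2, where sputum will be obtained".

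Under Eligibility Criteria, the microbiologically confirmed route is explained in parentheses as "sputum AFB smear positive by microscopy or +GeneXpert at entry". Clinical TB later confirmed by culture is listed as a separate route (b). TB participants must also meet the criterion "Initiating TB therapy within 30 days of enrollment".

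**The concern.** A death has a date. A culture conversion is known only to lie between the last positive and the first negative visit. Putting visit dates into a Cox model as if they were event times creates very large tied groups, and the common tie approximations handle these poorly. The last interval is the worst: it runs from week 8 to month 6, about 18 weeks, and most remaining conversions would fall in it.

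The analysis set raises a second issue. Only a person who starts culture-positive can convert. A participant who enters on smear or GeneXpert may have a negative baseline culture, especially if treatment has already begun. The 30-day criterion allows this, and the Recruitment section has staff searching registers for people within 30 days of TB treatment. Conversely, if the eligibility wording is taken literally, clinical cases proven by culture may fall outside the named population although they belong in the risk set.

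At stake are an understated effect and lost power on an outcome that the abstract names under its second aim.

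**Working it through.** **No figure to reproduce.** The protocol gives no effect size, median or power for culture conversion. The inputs are therefore the Table 3 visit schedule (weeks 2, 4, 8 and 26) plus assumptions: exponential conversion, control median 4 to 8 weeks, hazard ratio (HR) 1.25 to 2.0, full attendance, and 0 to 30% culture-negative at baseline.

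**Step 1: interval probabilities (control median 6 weeks, HR 1.5).** For an interval of w weeks, the conversion probability among those still positive is p0 = 1 − 0.5^(w/6) in control and p1 = 1 − 0.5^(1.5w/6) in the intervention arm.

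| Interval (weeks) | p0 | p1 | p1/p0 | ln(1−p1)/ln(1−p0) |
|---|---|---|---|---|
| 0–2 | 0.206 | 0.293 | 1.42 | 1.50 |
| 2–4 | 0.206 | 0.293 | 1.42 | 1.50 |
| 4–8 | 0.370 | 0.500 | 1.35 | 1.50 |
| 8–26 | 0.875 | 0.956 | 1.09 | 1.50 |

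The last column is what a complementary log-log model estimates, and it equals the true HR in every interval. The risk ratio p1/p0 falls toward 1 as intervals widen.

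**Step 2: Cox with Breslow ties.** The estimate θ solves Σ[d1 − (d0+d1)·θ·n1/(θ·n1+n0)] = 0. Per person randomised:
- at risk: n0 = 1, 0.794, 0.630, 0.397; n1 = 1, 0.707, 0.500, 0.250
- converting: d0 = 0.206, 0.164, 0.233, 0.347; d1 = 0.293, 0.207, 0.250, 0.239

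The d1 sum to 0.989. At θ = 1.296 the second term is 0.282 + 0.199 + 0.245 + 0.263 = 0.989, so θ is about 1.30. Breslow in effect averages the shrunken risk ratios.

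**Step 3: simulation with culture-positive participants only.**

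| True HR | Breslow | Efron | Grouped cloglog |
|---|---|---|---|
| 1.25 | 1.15 | 1.21 | 1.25 |
| 1.50 | 1.29–1.30 | 1.42 | 1.48–1.50 |
| 2.0 | 1.54–1.56 | 1.80–1.82 | 1.96–2.00 |

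The first row uses a control median of 6 weeks; the others span 4 to 8 weeks. A discrete logit, close to exact tie handling, gives about 1.66 at a true HR of 1.50. That figure is on an odds-ratio scale, so it does not recover 1.50 either.

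**Step 4: Kaplan-Meier.** At week 8, true conversion is 1 − 0.5^(8/6) = 0.603 in control and 1 − 0.5^(12/6) = 0.750 in the intervention arm, a difference of 0.147. The simulated visit-based difference is 0.144. Spacing makes the curve coarse between visits but does not shrink the contrast at shared visit times.

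**Step 5: baseline-negatives kept as week-2 converters (assumed rule).** With a 20% share, the week-8 difference becomes 0.8 × 0.147 = 0.118 (simulated 0.116). A true HR of 1.50 becomes about 1.33 (Efron), 1.22 (Breslow) or 1.37 (cloglog). Changing the model alone therefore does not cure this part.

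**Step 6: illustrative power (assumed 300 TB participants, HR 1.4).** Exact times give about 80%. Visit-dated times give 72–75% with Efron ties and 40–42% with Breslow.

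**The case against.** The strongest reply is that one condensed sentence in an article does not fix an ordinary Cox model. A discrete-time proportional hazards model could count as a similar survival method, and tie handling normally belongs in the analysis plan. This has some force: the protocol does not select Breslow, so the larger figures are a possibility and not the plan's stated choice. Under Efron, the shrinkage at HR 1.25 to 1.5 is only about 3 to 5% of the ratio. Still, the natural reading of the sentence is the Kaplan-Meier and Cox pair just described for mortality, and neither usual tie approximation recovers the hazard ratio.

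On the risk set, conversion ordinarily means positive to negative, a baseline culture is scheduled, and the Outcomes section refers to an Appendix 1, not shown, that defines Aim 2 outcomes further. In ordinary usage a positive culture is also microbiological confirmation, so the exclusion of route (b) is an ambiguity and not an established rule. Both points stand.

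Table 2 defines treatment failure by smear or culture at 5 months, so a programme result may sometimes exist between week 8 and month 6. It is not part of the Table 3 culture schedule.

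A reader might infer that the sparse visits also shrink the Kaplan-Meier comparison, or that culture-negative participants will be scored as converters. The documents support neither: both arms share the visits, and no such scoring rule is stated.

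Finally, conversion is not among the numbered hypotheses and has no row in Table 2. Both biases run toward no effect, so they would not create a spurious benefit.

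**Conclusion.** The point holds in limited form. Read naturally, the plan applies Cox regression to conversion times that fall into four tied intervals, and with usual tie handling this understates the hazard ratio: at a true 2.0, by about 9% (Efron) or 22% (Breslow). These sizes rest on exponential conversion, the assumed medians and full attendance. Common visit times in the two arms do not remove this bias, because it comes from the ties.

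The risk-set problem is conditional. The stated set does not require a positive baseline culture, but dilution arises only if culture-negative participants are kept and counted as converting. The 20% share used above is an assumption, and Appendix 1 may already settle the rule. The matter deserves correction before analysis, but it concerns a secondary outcome and does not touch the PEth primary analysis.

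**What to change.** Revise the conversion sentence in three respects:

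1. **Risk set.** Participants with a positive baseline culture, whatever their entry route, so that culture-confirmed clinical cases are included and baseline-negatives are not.
2. **Model.** A discrete-time model with complementary log-log link and one indicator per visit interval, keeping the planned random effects for site and counsellor; another interval-censored proportional hazards model would also serve.
3. **Display.** Cumulative conversion by arm at each culture visit, with the week-8 proportion reported explicitly.

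With assumed HR 1.50 and control median 6 weeks, the combined change recovers about 1.50. It needs no new data, since the baseline culture is already in Table 3, and the model is a standard binomial one. The cost is a revised sentence and a somewhat smaller risk set.
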